**Fig. 1 Fig1:**
[figure not shown]
TREASURE study design. ED SCLC patients with any response (defined as CR/PR or thoracic SD with CR/PR of extrathoracic lesions) after four cycles of standard chemo-immunotherapy consisting of carboplatin/etoposide and atezolizumab will be randomized to either receive thoracic radiotherapy or not. All patients will receive maintenance atezolizumab therapy until disease progression or occurrence of intolerable toxicities

**Table 1 Tab1:** Key inclusion and exclusion criteria of the TREASURE trial

Inclusion criteria	Exclusion criteria

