During treatment, tumor response will be assessed according to Response Evaluation Criteria in Solid Tumors (RECIST), version 1.1 by radiological imaging by computed tomography (CT) and/or magnetic resonance imaging (MRI) of the chest and upper abdomen at baseline, then every 6 weeks for the first 36 weeks, and every 9 weeks thereafter until occurrence of disease progression, according to the standard of care. After treatment discontinuation for reasons other than progressive disease, imaging will be performed accordingly to the above-mentioned schedule until progression, death, initiation of another anti-cancer therapy according to the standard of care or end of study. After the end of study, subjects will be proactively followed up regarding treatment-related adverse events until resolved, returned to baseline or deemed irreversible, until lost to follow-up, or withdrawal of study consent. All patients will be followed for survival. Follow-up by phone every 3 months (every 12 weeks [Q12W] ± 14 days) will be offered to patients who decline to return to the site for evaluations. The investigators of the study are responsible for the further treatment of the patient after the end of the study treatment for disease progression and shall support and advice the patients.

Safety assessment during this trial will include physical examinations, Eastern Cooperative Oncology Group (ECOG) performance status, clinical laboratory profile and continuous assessments of adverse events. The brief summary of all study procedures is presented in Table 2. An electronic case report form (eCRF) will be filled by the principal investigator or authorized study stuff person for each participant for data collection throughout the entire trial. The investigator must obtain written informed consent before patient participates in the clinical study. In addition, an adjudication committee has been established to exclude interstitial lung disease (ILD) in all pre-screened patients prior to study inclusion. All observed toxicities and side effects will be recorded in the eCRF and graded according to National Cancer Institute Common Terminology Criteria for Adverse Events (NCI-CTCAE) v5.0 for all patients and their relationship to all study treatment/ procedures assessed and summarized.

**Table 2 Tab2:** Schedule of assessments

Procedure/ Point in Time	Screening	Treatment				Post- Treatment		

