	Inclusion	C1D1	Each cycle (q2w ± 3 days)	Every second cycle (q4w ± 3 days)	EOT	Safety FU-1*	Safety FU-2**	FU (q12w ± 14 days)
Central review – ILD exclusion^#^	(x)							
Informed consent, eligibility criteria, demographics, medical and disease history	x							
Prior and Concomitant Medication Review	x	x	x		x			
Allocation/Randomization	x							
Vital Signs, O_2_ Saturation, and Weight	x	x	x		x	x	x	
ECOG Performance Status	x	x	x		x			
Pregnancy Test, CBC with Differential, Serum Chemistry Panel, Thyroid function test	x	x	x		x			
Urinalysis	x	Whenever clinically indicated						
12-lead ECG	x	Whenever clinically indicated						
Pulmonary function tests	x	x^a^		together with staging	x	x	x	
AEs	x	x	x		x	x	x	x
Full Physical Examination	x							
Directed Physical Examination		x	x		x	x	x	
FACT-L questionnaire	x	x		x	x	x	x	(x)
Tumor Imaging	x	(x^b^)		(x^c^)	(x^d^)			(x^d^)
Tissue	x	Optional: Re-Biopsy at time of progression						
Blood and stool	x	(x^e^)	x	x	x			
Atezolizumab administration		x	x					
Radiotherapy (Arm A^f^)		x						

^#^: A sponsor-independent adjudication committee was established to exclude interstitial lung disease (ILD) [Excl. criterion 5] in all pre-screened patients prior to study inclusion. All study sites are encouraged to provide tumor imaging in pseudonymize form during the (pre-)screening phase for the central review process

*: The regular 30-day full safety follow-up period (FU-1) begins on the day after the EOT visit and lasts approximately 30 days. The FU-1 visit occurs at or near the end of the 30-day safety follow-up period (±7 days)

**: The regular 90-day full safety follow-up period (FU-2) begins on the day after the EOT visit and lasts approximately 90 days. The FU-2 visit occurs at or near the end of the 90-day safety follow-up period (±7 days)

^a^: To be performed on C1D1 if in accordance with local standard

^b^: Chest X-ray to be performed on cycle 1 if in accordance with local standard

^c^: First on-study imaging to be performed 6 weeks (± 7 days) after baseline imaging. Further on-study imaging to be performed Q6W (42 days ±7 days) for the first 36 weeks, and every 9 weeks (±7 days) thereafter until occurrence of disease progression, according to the standard of care

^d^: Only applicable if EOT not according to already detected disease progression

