#### Sample size calculation

With *n =* 104 patients, under the assumption of a 20% improvement (from 52 to 72%) in the 12-month OS rate, a difference between treatment groups with regard to the primary endpoint OS can be detected with a power of 80% using a log-rank test at a two-sided alpha of 5%, assuming a dropout rate of about 10%, follow-up phase of 24 months, and an accrual period of 24 months. This improvement of 20% points corresponds to the effect of the radiation therapy together with the one mediated by ICI [2, 6]. Based on these assumptions, the resulting total sample size yielding the necessary number of 66 events is 92 patients (46 per arm) to achieve a power of 80%. In order to adjust for dropouts, *n =* 104 patients have to be randomized.

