#### Methods of statistical analysis

The primary efficacy analysis will be based on the intention-to-treat (ITT) population. Sensitivity analyses of the primary endpoint will be based on the per-protocol (PP) set. The primary endpoint will be analyzed by performing multivariable cox-regression adjusting for the variable therapy group and the stratification variables. The two-sided significance level is set to α = 0.05 (two-sided). Secondary endpoint analyses will be performed descriptively. Secondary endpoint analyses for group comparison include t-tests and chi-squared tests for continuous and ordinal or dichotomous variables, respectively. Feasibility will be analyzed by a description of absolute and relative frequencies of treatment withdrawal, which will be compared between treatment groups by chi-squared tests. Safety analysis will be done for all of the patients who received at least one dose of study medication and will comprise a description of relative and absolute frequencies of adverse events, severity grade based on the CTCAE Version 5.0. The adverse event summary tables will provide the number and percentage of patients with adverse events and the 95% Clopper-Pearson type confidence intervals for the event rates.

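### Adverse events are summarised as crude patient percentages although the observation period ends with progression or death, so late-accruing events would look more frequent in the radiotherapy arm if radiotherapy works

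*Protocol article*

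**What the plan says.** All of this is in the protocol article.

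- **Estimator (Methods of statistical analysis).** The AE summary tables give the "number and percentage of patients with adverse events and the 95% Clopper-Pearson type confidence intervals for the event rates".
- **Analysis set (same section).** "Safety analysis will be done for all of the patients who received at least one dose of study medication".
- **Group comparisons (same section).** Secondary endpoints are analysed descriptively. A general sentence adds: "Secondary endpoint analyses for group comparison include t-tests and chi-squared tests for continuous and ordinal or dichotomous variables, respectively". The sentences on safety themselves name no test between arms.
- **Length of treatment (legend of Fig. 1).** "All patients will receive maintenance atezolizumab therapy until disease progression or occurrence of intolerable toxicities". Study procedures likewise stops treatment at progression, unacceptable toxicity, patient request or end of study.
- **AE recording (Table 2).** The AE row is marked at screening, on day 1 of cycle 1, at each cycle, at EOT, at both safety follow-up visits and at the 12-weekly follow-up. The safety follow-up is counted from each patient's own EOT: "The regular 90-day full safety follow-up period (FU-2) begins on the day after the EOT visit and lasts approximately 90 days".
- **Survival follow-up (Study procedures).** "All patients will be followed for survival".
- **Expected effect (Sample size calculation).** The trial is sized "under the assumption of a 20% improvement (from 52 to 72%) in the 12-month OS rate", with 24 months of accrual and 24 months of follow-up.

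**The concern.** A crude percentage counts patients with at least one event, however long each was observed. Here the length of observation is set by progression and death, and a shift in survival is what the trial is sized to detect. If TRT works, arm A patients stay on treatment, on the visit schedule and alive for longer, and more of them will have had an event even when the risk per month is the same. If arm A had earlier progression or death, the same table would hide toxicity. The Clopper-Pearson interval covers sampling error around one common event probability. It does not correct for unequal observation, and the resulting percentage refers to no defined period.

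Safety and tolerability of the combination is a stated objective, and the safety endpoint lists many immune-mediated event types. Atezolizumab continues to progression, so such events can keep accruing. A successful trial could therefore appear to buy survival with extra toxicity that is partly only extra observation time.

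**Working it through.** **1. The plan's own figures.** With exponential survival, the hazard ratio is ln(0.72)/ln(0.52) = 0.502. The Schoenfeld formula gives 66.2 events for 80% power at two-sided 5%; the article states 66. The mean event probability is (0.620 + 0.849)/2 = 0.735, so 66/0.735 ≈ 90 patients are needed, against 92 stated. The sample size section is thus reproduced closely, and its survival assumptions can be carried forward. The article gives no AE percentages by arm to reproduce.

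**2. Inputs that the article does not give.** The AE hazard h is assumed constant and equal in both arms, at 1%, 2% or 4% per month. The control median on treatment is assumed to be 4 months. The ratio for time on treatment is taken as 0.73, the progression hazard ratio that the Background cites from an earlier phase III trial of TRT after chemotherapy.

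**3. AEs counted to EOT plus 90 days.** Time on treatment is exponential with rate λ, followed by 3 months of observation. The crude percentage is 1 − exp(−3h) · λ/(λ + h).

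- Arm B: λ = ln 2/4 = 0.1733 per month.
- Arm A: λ = 0.73 × 0.1733 = 0.1265 per month.
- Mean observation, 1/λ + 3: 8.8 months (B) and 10.9 months (A).

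| h per month | Arm B | Arm A | False excess |
|---|---|---|---|
| 0.01 | 8.3% | 10.1% | 1.8 points |
| 0.02 | 15.6% | 18.7% | 3.1 points |
| 0.04 | 27.9% | 32.6% | 4.7 points |

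For h = 0.02 in arm B: 1 − 0.9418 × 0.1733/0.1933 = 0.156. With a ratio of 1 in place of 0.73, the excess is 0 at every hazard.

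**4. Upper bound: AEs counted to death or study end.** Table 2 marks AEs at the 12-weekly follow-up too, so this reading is possible. The death rates are −ln(0.52)/12 = 0.0545 per month (B) and −ln(0.72)/12 = 0.0274 (A), with administrative censoring c uniform on 24–48 months. The crude percentage is the mean over c of h/(h + λ) · [1 − exp(−(h + λ)c)]. Mean observation is 15.6 months (B) and 22.6 months (A), a ratio of 1.45.

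| h per month | Arm B | Arm A | False excess |
|---|---|---|---|
| 0.01 | 13.8% | 19.6% | 5.7 points |
| 0.02 | 24.8% | 34.1% | 9.4 points |
| 0.04 | 40.6% | 53.5% | 12.9 points |

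**5. Fixed six-month window.** Cumulative incidence with death as competing event is h/(h + λ) · [1 − exp(−6(h + λ))], with the death rates of step 4. It gives 5.0% (B) against 5.4% (A), 9.7% against 10.4%, and 18.3% against 19.7%. The gap falls to 0.4–1.4 points.

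**6. Grade ≥ 3 pneumonitis.** Take the 2% of the article's non-toxicity scenario as the arm B crude rate under the upper-bound model of step 4. The same hazard then gives 2.9% in arm A. The excess is 0.9 points, or 0.009 × 52 ≈ 0.5 of a patient in an arm of 52.

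**The case against.** The strongest case against is that the section states nothing false. Number, percentage and exact interval form the customary first AE table; the text calls it a description, names no AE test between arms, and does not exclude other summaries. Exposure-adjusted rates are often left to a statistical analysis plan, which is not shown. All AE hazards above are assumed, and the larger figures need a risk that stays constant long after treatment has stopped.

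Much of this stands. The tables are descriptive, no decision or error rate depends on them, and the analysis plan may already add what is proposed here. The size of the effect rests on assumptions, and the 6–13 points are a bound, not an expectation. What remains is that the article does fix an estimator and an interval for AEs, and that this estimator gives a distorted picture between arms under the effect for which the trial is sized.

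Two stronger readings are tempting. A reader might infer that arm A must look more toxic by construction. The documents do not support that: the excess exists only if time to progression or death differs between arms. A reader might also infer that the pneumonitis assessment is compromised. It is not, to any material degree. Early radiation toxicity falls in a period when nearly all patients in both arms are still observed, and the interim rule uses its own 12-week window after TRT, in arm A only.

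**Conclusion.** The point holds as a moderate one about the choice of AE summary. With equal AE hazards of 1–4% per month, a 4-month control median on treatment and a ratio of 0.73 for time on treatment, the crude tables would show a false excess of about 2–5 points in arm A when AEs are counted to EOT plus 90 days. Constant risk to death or study end under the plan's survival assumptions gives an upper bound of about 6–13 points. The direction follows from longer observation in arm A; the size depends on the assumed hazards and treatment times. The distortion concerns late or steadily accruing events, such as immune-mediated ones, and vanishes without a difference in time to progression or death. The primary analysis and the safety stopping rule are unaffected.

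**What to change.** Keep the crude tables with their Clopper-Pearson intervals as a listing. Base between-arm AE statements on cumulative incidence (Aalen-Johansen, death as competing event) at a fixed time from randomization, for example 6 months, with 95% confidence intervals. Add exposure-adjusted rates per patient-month for later events. State up to which visit AEs count, since Table 2 allows both EOT plus 90 days and the 12-weekly follow-up; patients who stop treatment early reach month 6 only through the latter.

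The cost is a change of analysis wording and a few extra tables. The dates needed are those of AE onset, EOT and death; no visits or patients are added. The downside is that the fixed window leaves late events to the exposure-adjusted table, which itself assumes a roughly constant rate over the period it covers.

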### Trial status

As of January 2022, 19 study sites (18 in Germany, 1 in Austria) are initiated. The first patient was enrolled on 28th July 2020. The TREASURE trial is currently recruiting patients.

## Discussion

Despite recent advances in therapeutic landscape of treatment of SCLC, survival rates are still poor and new treatment options are required. The phase II TREASURE study is designed to examine efficacy and safety of the addition of TRT to atezolizumab maintenance therapy in patients who have responded to an induction chemo-immunotherapy.

The Phase II DETERRED trial has demonstrated safety of combining atezolizumab with thoracic radiation in NSCLC patients at even higher total doses than in the current TREASURE protocol [13], and other trials in different solid tumors also support that combination of immunotherapeutic drugs and radiotherapy is safe and well tolerated [14–16]. However, there is still a certain overlap in toxicities observed in the combination treatment. As numerous clinical investigations have shown that dosimetric parameters, such as V20, V30, and mean lung dose, can reduce the risk of lung damage, the proposed radiation protocol applied in this trial has been designed accordingly to reduce the risk of pneumonitis events induced by thoracic radiation therapy. Additionally, in order to enroll only patients with sufficient pulmonary resources to persevere a pneumonitis, inclusion and exclusion criteria include cut-offs for pulmonary function and exclude oxygen-dependent patients from this trial. Nevertheless, considering the possible risk of a higher rate of pneumonitis events in the combinatorial treatment group, a safety interim analysis will be performed in this arm. Furthermore, an accompanying translational research program will address questions regarding the effect of radiotherapy on the immunological status of the tumor and will explore biomarkers, which are much needed for checkpoint blockade with and without concurrent radiotherapy in SCLC patients. In summary, the TREASURE trial will help to gain deeper insight into the interplay between immunotherapy and radiotherapy, and, thus, extend the therapeutic options for ED SCLC patients. Patient recruitment for the TREASURE trial started in September 2020, and participating facilities across Germany and Austria are currently enrolling patients who match the eligibility criteria.

## Data Availability

Data generated by this study will be available for access from the corresponding author upon reasonable request.

## Abbreviations

AE: Adverse event
AIO: Arbeitsgemeinschaft Internistische Onkologie
CR: Complete response
CRF/ eCRF: Case report form / electronic case report form
CRT: Chemoradiation therapy
CT: Computed tomography
CTCAE: Common terminology criteria for adverse events
CTV: Clinical target volume
ECG: Electrocardiogram
ECOG: Eastern Cooperative Oncology Group
ED: Extensive disease
EOT: End of treatment
FACT-L: Functional Assessment of Cancer Therapy - Lung
FU: Follow-up
GTV: Gross tumor volume
Gy: Gray
HR: Hazard ratio
ICI: Immune checkpoint inhibitors
ILD: Interstitial lung disease
ISMB: Independent safety monitoring board
ITT: Intention-to-treat
IWRS: Interactive Web Response System
MHC I: Major histocompatibility complex
MRI: Magnetic resonance imaging
NSCLC: Non-small cell lung cancer
OS: Overall survival
PCI: Prophylactic cranial irradiation
PD-1: Programmed death-1
PD-L1: Programmed death- ligand 1
PET: Positron emission tomography
PFS: Progression-free survival
PP: Per-protocol
PR: Partial response
PTV: Planning target volume
Q3W: Every 3 weeks
Q12W: Every 12 weeks
R: Randomization
RECIST 1.1: Response evaluation criteria in solid tumors, version 1.1
SAE: Severe adverse event
SCLC: Small cell lung cancer
SD: Stable disease
SMC: Safety Monitoring Committee
TRT: Thoracic radiotherapy
